**Methods:**

Our proposed study has formative and experimental activities across the four phases of the Exploration, Preparation, Implementation, and Sustainment (EPIS) framework. Through an implementation mapping conducted with stakeholders in the exploration phase, we identified a core package of IS (Core) and an enhanced package of IS (Core+) mostly selected from the Expert Recommendations for Implementing Change. In the preparation phase, we refined and tailored the Core and Core+ IS with the implementation resource teams for local appropriateness. In the implementation phase, we will conduct a cluster-randomized hybrid type III trial to assess the comparative effectiveness of Core versus Core+. HIV comprehensive treatment sites (*k* = 12) will be matched by region and randomized to Core or Core+ in the ratio of 1:1 stratified by region. In the sustainment phase, we will assess the sustainment of CCST at each site. The study outcomes will be assessed using RE-AIM: reach (screening rate), adoption (uptake of IS by study sites), IS fidelity (degree to which the IS occurred according to protocol), clinical intervention fidelity (delivery of CC screening, onsite treatment, and referral according to protocol), clinical effectiveness (posttreatment screen negative), and sustainment (continued integrated CCST service delivery). Additionally, we will descriptively explore potential mechanisms, including organizational readiness, implementation climate, CCST self-efficacy, and implementation intentions.

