2	CCST intervention fidelity (EPIS inner context)	•% WLHIV with preinvasive cancer eligible for treatment who had same-day treatment •% WLHIV treated for preinvasive cancer who had posttreatment follow-up screening at 12 months •% WLHIV with suspected cancer or lesions ineligible for treatment referred	Health records Participant survey
2	Organizational readiness for CCST	•(QUANT) organizational readiness for implementation (ORIC)	Provider survey
2	Implementation climate (EPIS inner context)	•(QUANT) six items with three subscales, degree that CCST is expected, supported, and rewarded	Provider survey

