### Data analysis

Preliminary analyses will begin with an examination of the distribution of variables to assess and describe their characteristics (means, standard deviations, quartiles, ranges, frequencies, and percentages) for overall and for Core and Core+ groups separately and to allow assessment of randomization. Randomization will be tested by performing a series of Wilcoxon rank-sum tests for continuous variables and chi-square (or Fisher’s exact) tests for categorical variables to compare the groups on baseline demographic and clinical variables. Variables on which the groups differ initially will be explored as covariates in subsequent analysis. Intent-to-treat analysis will be conducted as the primary analysis. All estimates (point estimates and 95% confidence intervals) for the study outcomes will be adjusted by the cluster effect of clinics as described below.

The screening rate (primary outcome) will be summarized by frequency and proportion. A generalized linear mixed-effect model (GLMM) [73] with a binomial link will be used to examine the difference in screening rate (reach outcome) between Core and Core+. A random intercept will be included in the model to account for the cluster effect of the site. Multivariable random effects models will be used to examine the impact of covariates on estimated intervention effects. The GLMM will be also used to compare secondary outcome measures related to adoption, implementation strategies fidelity, and clinical intervention fidelity between two intervention groups, with a binomial link for a binary outcome and a Gaussian link for a continuous outcome. The ICM, MISII, and Self-Efficacy/EBP Beliefs Scale data collected from providers will also be analyzed similarly using the GLMM.

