#### Covariate prescreening and variable selection procedure

In the multivariable model described above, adjustments are typically made to correct for baseline imbalances between groups and to adjust for variables known to influence the outcome independent of the intervention. Baseline characteristics will be pre-screened and assessed for an imbalance between the two intervention groups (Wilcoxon rank-sum test or Fisher’s exact test) and their association with the outcome (univariable mixed-effects model). Only those variables found to be moderately associated (*p* < 0.15) with the outcome or imbalanced (*p* < 0.10) between groups will be considered as potential covariates in the initial multivariable model. Backward elimination of insignificant variables will be used to select the main effects in the final model; all covariates that are significant at *p* < 0.10 will be kept in the final model.

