### Schedule of measurement

We will collect baseline data on the potential mechanisms (ORIC and MISII) and CC screening rates among WLHIV in the 12 facilities (Figure 5). In aim 2, each participant will be assessed at 12 months after enrollment for the receipt of CC screening (study M33). Treatment of precancerous lesions and referral of suspected cancer or lesions ineligible for treatment will be assessed at 12 and 18 months after enrollment (study M33 and M39). Posttreatment follow-up screening will be assessed at 27 and 33 months after recruitment (study M48 & M54). Data on specific potential mechanisms will be collected from the healthcare providers after recruitment and then 6 months, 12 months, and annually.

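### Baseline MISII is collected, but the model stated for follow-up MISII does not fix it as a covariate; it can enter only through p-value screening

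*Protocol article*

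**What the plan says.** **Collection.** Under Schedule of measurement the Protocol article states: "We will collect baseline data on the potential mechanisms (ORIC and MISII) and CC screening rates among WLHIV in the 12 facilities". It adds: "Data on specific potential mechanisms will be collected from the healthcare providers after recruitment and then 6 months, 12 months, and annually".

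**Model.** Under Data analysis for Aim 2, reach is compared between arms in a GLMM, and "A random intercept will be included in the model to account for the cluster effect of the site". Multivariable versions are to examine covariates, and continuous outcomes get the Gaussian form. The provider scales are then covered by one sentence: "The ICM, MISII, and Self-Efficacy/EBP Beliefs Scale data collected from providers will also be analyzed similarly using the GLMM". It names no baseline score, and ORIC is not in its list.

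**Covariates.** Under Covariate prescreening and variable selection procedure: "Baseline characteristics will be pre-screened and assessed for an imbalance between the two intervention groups". A variable is considered if it is associated with the outcome at p < 0.15 or imbalanced between arms at p < 0.10. After backward elimination, "all covariates that are significant at *p* < 0.10 will be kept in the final model".

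**Status of the measures.** The abstract says: "Additionally, we will descriptively explore potential mechanisms, including organizational readiness, implementation climate, CCST self-efficacy, and implementation intentions". Table 3 lists readiness (ORIC) as a quantitative Aim 2 measure from the provider survey.

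**The concern.** Staff intention to use screening and treatment exists before any strategy starts and is likely to differ between clinics. With six sites per arm, a chance difference at baseline can be sizeable, and a follow-up comparison that ignores it carries that noise in its interval. The usual remedy is to adjust for the baseline value of the same scale, chosen in advance. Here the baseline is planned, yet nothing commits the analysis to using it.

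If the selection rule covers baseline MISII, the covariate most likely to be prognostic must earn its place by p-value in what may be a few dozen providers. If the rule does not cover it, no stated route admits it. At stake is the precision of one mechanism comparison, and whether its final model is known in advance.

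**Working it through.** **1. The plan's own figure.** The article gives no power, SD, ICC, provider number or baseline-to-follow-up correlation for MISII. Its only power figures are for reach: 14% v 34%, 6 sites per arm, 200 women per site, two-sided 0.05.

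- Design effect = 1 + 199 × ICC, which is 12.94 at ICC 0.06 and 14.93 at 0.07.
- SE = sqrt[(0.14 × 0.86 + 0.34 × 0.66) × design effect / 1200], which is 0.0610 and 0.0655.
- A noncentral t on 10 df gives 84.0% and 78.6%, matching the stated 84% and 78.6%.
- At ICC 0.02 it gives 99.7%, against a stated value above 99.9%.

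These figures concern a different outcome and do not bear on this point. They do show that a t reference on 10 between-site df matches the plan's own calculation, so the same reference is used below.

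**2. Effect of adjustment on interval width.** Let r be the correlation between baseline and follow-up MISII, assumed equal at site and provider level. Adjustment multiplies the variance of the arm difference by 1 − r² and takes one between-site df (10 to 9). The width ratio, adjusted to unadjusted, is

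(t₀.₉₇₅,₉ / t₀.₉₇₅,₁₀) × sqrt(1 − r²) = (2.262 / 2.228) × sqrt(1 − r²) = 1.015 × sqrt(1 − r²).

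| r | Width ratio | Change |
|---|---|---|
| 0.1 | 1.010 | 1% wider |
| 0.3 | 0.969 | 3% narrower |
| 0.5 | 0.879 | 12% narrower |
| 0.7 | 0.725 | 27% narrower |

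Break-even: r = sqrt[1 − (2.228/2.262)²], about 0.17. The ratio does not depend on the ICC or the number of providers.

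**3. The same in scale units.** Assume ICC 0.10 and m = 3 or 4 providers per site (the number the article gives for the Aim 3 survey, borrowed here). The variance of a site mean in SD² units is ICC + (1 − ICC)/m, which is 0.400 or 0.325. The unadjusted 95% half-width is 2.228 × sqrt(2 × variance / 6), which is 0.81 or 0.73 SD. At r = 0.5 it becomes 0.72 or 0.65 SD.

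**4. Illustrative power.** Assume m = 4, ICC 0.07 (top of the plan's range for screening) and a true difference of 0.8 SD. Power is 62.3% unadjusted, then 65.3% at r = 0.3, 73.6% at r = 0.5 and 88.0% at r = 0.7. Every input apart from the six sites per arm and the two-sided 0.05 level is assumed.

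**5. How often the screen would keep the baseline anyway.** This was simulated as a simple correlation test at p < 0.10, ignoring clustering.

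| r | Kept, n = 36 | Kept, n = 48 |
|---|---|---|
| 0.3 | 56% | 67% |
| 0.5 | 94% | 98% |

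So if the selection rule does apply to baseline MISII, much of the gain in step 2 is already obtained at r = 0.5. The step 2 figures are the gain over a model in which the baseline never enters.

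**The case against.** The strongest reply is that the article is silent and excludes nothing. The cross-reference to the reach model can be read to include the multivariable models in the same paragraph, and a baseline scale score can count as a baseline characteristic under the selection rule. That stands. A reader might infer that the plan compares MISII with its baseline left out; the text does not say so.

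Second, the rule tends to keep the covariate when it matters and lose it mainly when little is at stake (step 5). That also stands, and it shrinks the practical loss. It does not make data-driven selection the better choice: the final model stays unknown until the data are seen, and fixing the covariate costs almost nothing.

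Third, a reader might infer that precision is lost for ORIC as well. The documents do not support this. The abstract promises a descriptive look at readiness and no ORIC arm comparison is stated, so no planned comparison loses anything. How ORIC will be summarised is simply not spelled out.

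Fourth, a reader might take chance baseline differences as bias in favour of or against Core+. An unadjusted comparison of randomised sites is imprecise, not biased, and its interval already reflects such differences.

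Finally, covariate lists for exploratory scales are often left to the analysis plan. That is fair for detail in general. Here, though, the article does fix a covariate rule, and it is that rule, with no exemption for a baseline score, that is worth changing.

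**Conclusion.** The point holds as a modest improvement. The article plans baseline MISII and commits follow-up MISII to a model, but offers the baseline score no route except p-value selection. Naming it in advance is the better method.

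The size is conditional. The range runs from about 1% wider at r = 0.1 to about 27% narrower at r = 0.7. It assumes equal r at both levels, a baseline that would otherwise not enter, and, for the provider-level part of the gain, the same staff answering twice. The article states none of these.

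The consequence is limited to an exploratory mechanism measure. Reach, its power and the main conclusion do not change.

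**What to change.** In Data analysis (Aim 2), add that follow-up MISII is compared between arms in the linear mixed model with a site random intercept and baseline MISII as a pre-specified fixed covariate. Use the provider's own baseline score, or the site-mean baseline where staff have changed. State that this covariate is exempt from the prescreening and backward elimination. If ORIC is also to be compared between arms, treat it the same way; if not, a clause saying it will be summarised descriptively is enough.

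The cost is wording only, with no new data. The statistical price is at most one between-site degree of freedom, about 1% in interval width at r = 0.1 and 1.5% if the baseline carries no information at all.

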#### Covariate prescreening and variable selection procedure

In the multivariable model described above, adjustments are typically made to correct for baseline imbalances between groups and to adjust for variables known to influence the outcome independent of the intervention. Baseline characteristics will be pre-screened and assessed for an imbalance between the two intervention groups (Wilcoxon rank-sum test or Fisher’s exact test) and their association with the outcome (univariable mixed-effects model). Only those variables found to be moderately associated (*p* < 0.15) with the outcome or imbalanced (*p* < 0.10) between groups will be considered as potential covariates in the initial multivariable model. Backward elimination of insignificant variables will be used to select the main effects in the final model; all covariates that are significant at *p* < 0.10 will be kept in the final model.

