#### Randomization

The unit of randomization will be the sites. Each site represents a cluster in the randomization representing the clinic site and the WLHIV receiving treatment at the site. We will conduct simple random allocation with the sites randomized to either the Core or Core+ IS. There are six geographic regions in Nigeria, and sites will first be matched by region, and then each site in a matched pair will be randomized to Core or Core+ IS. A random number generator will be used to assign the sites. A flow diagram for the randomization and intervention allocation is shown in Figure 3. The healthcare workers and the patients will be blinded to whether their sites are allocated to the core package of IS or an enhanced package of IS.

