### Sample size and power calculation

We examine the sample size for the primary implementation outcome of “reach,” indicated by the CC screening rate in WLHIV. Based on preliminary data from previous studies, we assumed a conservative screen rate of 14% in the core implementation strategy group [70]. We plan to enroll 12 sites (6 sites per intervention group). Hade et al. [71] reported the range of intraclass correlation (ICC) fall in 0.02–0.07 in the group-randomized breast and CC screening studies. We performed a sensitivity analysis by assuming a range of ICC of 0.02–0.07 for site cluster effect on the outcome and a feasible sample size of 200 subjects per site. We estimated that we could achieve at least 80% power for ICC of 0.02–0.06 (84% for *ICC* = 0.06 and > 99.9% for *ICC* = 0.02) to detect a minimum improvement of 20 percentage points in screening rate (that is, 34% screening rate) in Core+ group using a two-sided type I error of 0.05, and we could still achieve 78.6% power for *ICC* = 0.07. The 34% screening rate is achievable and a conservative estimate for the Core+ group based on our prior related work [61]. The power analysis was conducted using the statistical software R package *cluster Power* [72].

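### Baseline balance is tested as if about 2,400 women had been randomised individually, so the p<0.10 screen cannot judge the randomisation and inflates the candidate list for a data-chosen adjusted model

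*Protocol article*

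**What the plan says.** Under Randomization the protocol article states: "The unit of randomization will be the sites". It adds that "sites will first be matched by region, and then each site in a matched pair will be randomized". The sample size section plans six sites per arm and "a feasible sample size of 200 subjects per site".

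Under Data analysis for Aim 2: "Randomization will be tested by performing a series of Wilcoxon rank-sum tests for continuous variables", with chi-square or Fisher tests for categorical variables. Variables that differ between the arms are then to be explored as covariates. The same section promises adjustment for clustering, but only for the estimates of the study outcomes.

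The covariate section repeats the balance check: "Baseline characteristics will be pre-screened and assessed for an imbalance between the two intervention groups", again by Wilcoxon or Fisher test. A variable enters the initial multivariable model if it is imbalanced at p<0.10, or if it is associated with the outcome at p<0.15 in a univariable mixed-effects model. Then: "Backward elimination of insignificant variables will be used to select the main effects in the final model", keeping those with p<0.10.

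**The concern.** Wilcoxon, chi-square and Fisher tests take each woman as an independent observation. Randomising sites does not make women in different arms exchangeable one by one. It makes the sites exchangeable, within pairs. When women at a site resemble each other, the variance of a difference between arms exceeds what these tests assume, and small p-values appear far more often than their nominal level.

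Two uses of these p-values are at stake. The plan presents them as a test of the randomisation, which they cannot be at these error rates. They also form one of two routes into the adjusted model, whose content is then settled by further p-values instead of by prior knowledge of what predicts screening. The other route, the outcome-association screen, does use a mixed model, so the plan handles clustering in one half of the prescreen and not in the other.

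**Working it through.** **Inputs from the protocol article.** 12 sites, 6 per arm; m = 200 women per site, so 1,200 per arm and 2,400 in all; for the ICC, the sample size section speaks of "assuming a range of ICC of 0.02–0.07 for site cluster effect on the outcome"; screening 14% against 34%; two-sided alpha 0.05. No ICC is given for baseline variables. The outcome range is borrowed for them, and lower values are shown as well.

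**The plan's own power first.** Design effect DE = 1 + (m − 1) × ICC = 1 + 199 × ICC. Standard error of the difference = √[(0.14×0.86 + 0.34×0.66) × DE / 1,200] = √[0.3448 × DE / 1,200]. Power is taken from a noncentral t with 2 × (6 − 1) = 10 degrees of freedom.
- ICC 0.06: DE 12.94, power 84.0% (stated 84%).
- ICC 0.07: DE 14.93, power 78.6% (stated 78.6%).
- ICC 0.02: DE 4.98, power 99.7% (stated above 99.9%; a normal approximation gives 99.96%).

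So the cluster size, number of sites and design effect used below are those behind the plan's own power.

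**False-flag rate of a test that ignores site.** With no true difference, the test statistic has variance of about DE instead of 1. The chance of p < α is 2 × [1 − Φ(z / √DE)], with z = 1.645 for α = 0.10 and z = 1.960 for α = 0.05. For example, at ICC 0.02: 1.645 / √4.98 = 0.737, giving 46%.

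| ICC | DE | flagged at p<0.10 | flagged at p<0.05 |
|---|---|---|---|
| 0.005 | 2.0 | 24% | 17% |
| 0.01 | 2.99 | 34% | 26% |
| 0.02 | 4.98 | 46% | 38% |
| 0.03 | 6.97 | 53% | 46% |
| 0.05 | 10.95 | 62% | 55% |
| 0.06 | 12.94 | 65% | 59% |
| 0.07 | 14.93 | 67% | 61% |

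The p<0.10 rate reaches one half when √DE = 1.645 / 0.6745. That is DE = 5.95 and ICC = 4.95 / 199 = about 0.025.

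**Check by simulation.** In 3,000 null trials per ICC, with an assumed 30% prevalence for the binary covariate, the p<0.10 flag rates were 46% (Wilcoxon) and 46% (Fisher) at ICC 0.02, and 65% and 67% at 0.07. A t test on the 12 site means flagged 9.3% to 10.7% over ICC 0 to 0.07, close to the nominal 10%.

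**Following the selection to its end.** 500 null trials with 10 pure-noise covariates each were passed through both screens and the backward elimination:

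| ICC | entered initial model | kept in final model | type I error, unadjusted | type I error, adjusted |
|---|---|---|---|---|
| 0.02 | 52% | 9.6% | 4.0% | 3.8% |
| 0.06 | 70% | 10.1% | 4.2% | 4.0% |

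This used a linear mixed-model approximation with known ICC and no pairing, and the type I figures carry a simulation error of about √(0.04×0.96/500) = 0.9 percentage points. It is indicative only.

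**The case against.** The best defence is that little of this reaches the primary comparison. Being flagged only makes a variable a candidate. The multivariable models carry random effects, and elimination at p<0.10 clears out most false candidates. In the simulation about one noise covariate in ten stayed, and type I error for the arm effect was about 4% with or without selection. This stands, and it rules out several stronger readings that a reader might infer:

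- *That most baseline variables will be flagged by chance.* This needs a baseline ICC above about 0.025. The documents give an ICC for the outcome only. Sites are also paired by region and matched on facility type, which the formula ignores and which could lower the relevant between-site variance.
- *That noise chooses the final adjusted model.* Elimination removes most of what the balance tests falsely add.
- *That the treatment effect is read from the selected model.* The Data analysis section first gives a random-intercept GLMM for the comparison of screening rates. It then adds multivariable models to see how covariates affect the estimated effect. The selected model may well be supplementary; the text does not say plainly which one is primary.
- *That the trial will announce a failed randomisation.* The only planned consequence of a difference is exploration as a covariate.

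The defence does not rescue the tests themselves. The article names the tests, the thresholds and the elimination rule, so this is a stated rule that does not fit the design, not detail left to an analysis plan.

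**Conclusion.** The point holds in a limited form. The baseline tests have the wrong unit of analysis. Over the plan's own outcome ICC range, a nominal 10% test has a false-flag rate of 46% to 67%, or 4.6 to 6.7 times nominal. Even at ICC 0.005 to 0.01 it is 24% to 34%. These figures rest on borrowing the outcome ICC for baseline variables and on ignoring the region pairing.

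It follows that the tests cannot assess the randomisation and that they inflate the candidate list. No harm to the type I error of the arm comparison was shown. What remains in the final model is a selection problem. Its covariates are chosen from the trial data, and no covariate is protected. The site's baseline screening rate, which the Schedule of measurement says will be collected, can be dropped for p≥0.10, although a site-level covariate with 12 sites has little chance of reaching significance even when it matters.

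**What to change.** - Delete the baseline significance tests, the p<0.15 and p<0.10 screens and the backward elimination.
- Describe baseline balance by arm and by site, without p-values.
- Before outcomes are seen by arm, fix a short covariate list, for example age and the site's baseline screening rate, and keep it whatever its p-values.
- State which GLMM, with or without these covariates, gives the primary estimate, and how the region pairing enters it.

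This is a change of wording, with no new data and no change in sample size. It does have a statistical cost, because each site-level covariate uses degrees of freedom from 12 sites. Intercept, arm and baseline rate leave 12 − 3 = 9. Adding region as fixed effects (five parameters) leaves 12 − 8 = 4. Site-level covariates must therefore be few, and the handling of the region pairs should be chosen with that limit in view. A woman-level covariate such as age costs little in this respect.
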